### Procedure

The procedure for this study is shown in Fig 2. Participant ID numbers were randomly assigned to the benign or pain modification group before data collection began via Random.org. After having read the information sheet and signed the consent form, participants completed the self-report measures. Following this, participants completed the heat pain-threshold task. Next, participants completed the Ambiguous Scenarios Task aiming to modify their biases towards pain-related or benign interpretations of ambiguous stimuli, according to their randomised group. This was immediately followed by the test phase of the Ambiguous Scenarios Task, then the Incidental Learning Task and the Sentence Generation Task. Participants then completed the ISSA. At the end of the experiment, participants in the pain-related CBM-I group completed 30 trials of the benign modification to ensure that they did not experience lasting effects of pain-related bias modification, before being thanked and debriefed. The entire experimental duration was approximately 90 minutes.

**Fig 2 pone.0318296.g002:**
[figure not shown]
A flowchart showing the experimental procedure for the pilot study and main study exploring the effects of pain-related interpretation bias modification on interpretation of ambiguous somatosensory and linguistic stimuli in healthy individuals (shaded components show main study differences to the pilot study).

### Data reduction and analytic plan

Data was analysed using RStudio version 1.3.1073 [49] with R version 4.0.2 [50]. As this is a pilot study, descriptive statistics and Cohen’s *d* effect sizes only are reported. Pearson’s correlation coefficients were also computed across all participants between self-report measures with measures of interpretation bias and interpretation of somatosensory sensations using the R package ‘corrplot’ [51]. Self-report measures were scored according to their published instructions. For the Ambiguous Scenarios Task, the proportion of correct comprehension questions was calculated to determine engagement with the task. Mean scores for each category of ending were calculated for each participant. The mean score for benign target endings was be subtracted from the mean score for negative endings to give an index of biased interpretation, as in previous use of the Ambiguous Scenarios Task [52]. A positive interpretation bias index indicates pain-related interpretation bias.

Ambiguousscenariosindex=TN−TB

Where *TN* =  mean score for target negative endings and *TB* =  mean score for target benign endings.

For the Incidental Learning Task, trials with incorrect or no response were excluded (learning phase: 1.39%, testing phase: 1.54%). Histograms and boxplots showed that response times less than 200ms or greater than 800ms were outliers, so these were removed (learning phase: 1.00%, testing phase: 1.08%). Response times more than three standard deviations outside each participant’s mean response time were excluded (learning phase: 1.70%, testing phase: 1.54%). The congruency effect was calculated with data from the learning phase. A positive congruency effect indicates a faster response when the dot appears on the predicted side of the screen, indicating that the contingency has been learnt.

Congruencyeffect=RTi−RTc

Where *RTi* =  mean response time on incongruent trials and *RTc* =  mean response time on congruent trials. The IB index was calculated from response times in the test phase, as in previous research [18,53]. A positive index indicates pain-related interpretation bias.

Interpretationbiasindex=RTn−RTp

Where *RTn* =  mean response time to targets in the location associated with neutral words and *RTp* =  mean response time to targets in the location associated with pain words.

For the Sentence Generation Task, sentences were categorised as pain-related or benign. The definition for pain-related interpretations was: ‘describes a painful experience or a situation usually associated with pain’; the working definition for benign interpretations was: ‘describes an experience or situation unrelated to pain’ [44,54]. The proportion of pain-related sentences out of total sentences generated was calculated, as in previous research [17].

For the ISSA, mean ratings of intensity and unpleasantness were calculated for each stimulus intensity. Ratings were excluded where the temperature required for the percentage of pain threshold could not be reached due to the safety limits of the TSA-II.

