### Stimuli and experimental paradigms

#### Stimuli.

The Ambiguous Scenarios Task used stimuli developed by Jones and Sharpe [10], with adjustments made to account for differences between Australian and British English. Specifically, ‘capsicum’ was changed to ‘pepper’, ‘sun-baking’ to ‘sun-bathing’, and ‘solarium’ to ‘sunbed’ (S1 File). Ambiguous pain-related words and neutral homographs were used in the Sentence Generation Task. Pain homographs had sensory-pain and neutral meanings, and were derived from the McGill Pain Questionnaire [41]. Neutral homographs had multiple neutral meanings. The neutral and pain homographs were matched on length and written frequency according to the MRC Psycholinguisic Database [42] and on number of strong associations according to the University of Florida Free Association Norms Database [43]. For the training phase of the Incidental Learning Task, unambiguous sensory-pain words and neutral homographs were used (the latter were the same as those used in the sentence generation task; although they have multiple meanings, none of these were pain-related and so were suitable as neutral training stimuli). Ambiguous words with sensory-pain and neutral meanings were used in the testing phase of the Incidental Learning Task. These stimuli have previously been used in attention, interpretation and memory bias research from our lab [44,45], and are shown in Table 1.

**Table 1 pone.0318296.t001:** Sensory-pain and neutral words used in the sentence generation task and the incidental learning task.

Ambiguous words with sensory-pain and neutral meanings	Neutral homographs with multiple meanings	Unambiguous pain words
Tension	Setting	Aches
Pounding	Boarding	Harmful
Pressing	Inclined	Painful
Splitting	Promotion	Hurting
Piercing	Animated	Pinching
Drilling	Compound	Stinging
Tight	Grasp	Headache
Pulsing	Banking	Soreness
Squeeze	Trailer	Agonising

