#### Sentence generation task.

This is a direct measure of interpretation bias, which has been successfully implemented in previous research from our research group [44,45]. The task included 18 experimental trials featuring nine ambiguous sensory-pain and nine ambiguous neutral stimuli [44]. Trials were presented in a new randomised order for each participant. Each trial began with a fixation cross for 1000ms. A single word replaced the cross, presented in size 40 Times New Roman font which remained on the screen until the end of the trial. Participants read the word and used a keyboard to type a single sentence featuring the word once. Text appeared in size 18 Times New Roman font below the experimental word as the participant typed. Backspace and delete keys were used to correct spelling mistakes or make amendments as necessary, and the F12 key was used submit the response. The next trial began after 120 seconds if no response was submitted. Trials followed one another automatically, with all 18 trials presented in a single block. Two practice trials were initially presented to familiarise participants with the requirements of the task, featuring the words *running* and *dancing*. This task took approximately 15 minutes to complete.

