Descriptive statistics will be computed for demographic characteristics, self-report measures (scored according to their instructions), cognitive bias task scores (Ambiguous Scenarios Task test phase, Sentence Generation Task, Visual-Probe Task and free recall task) and responses on the Interpretation of Ambiguous Somatosensory Sensations Task. Differences between the benign and pain modification groups will be conducted using independent samples *t*-tests and mixed-design ANOVAs where appropriate. Should any statistically significant differences be observed between groups on demographic or self-report measures, analyses will be conducted controlling for these (e.g., Analysis of Covariance). Pearson’s correlation coefficients will be conducted between outcomes on the self-report measures, cognitive bias scores and interpretation of ambiguous sensations ratings. As thermal pain sensitivity is associated with age (e.g., [88–90]), Pearson’s correlation coefficients will also be computed between age and interpretation of ambiguous sensations ratings. Should these be statistically significant, then age will be controlled for as a covariate where appropriate in the statistical analyses. The moderating effects of visual imagery and intolerance of uncertainty on the association between group and interpretation bias scores from the Ambiguous Scenarios Task will be investigated using linear multiple regression models. Similarly, linear multiple regression models will be used to test the effect of group on interpretation bias measures while controlling for other variables that differ between groups.

Data from the Ambiguous Scenarios Task, Sentence Generation Task and ISSA will be processed as discussed above for the pilot study. The only difference is that for the Sentence Generation Task, two raters will independently and blindly categorise participant response sentences as either pain-related (e.g., *He had a pressing pain in his head*) or benign (e.g., *The boy was pressing the buttons in the lift*). The initial inter-rater agreement will be computed, and any disagreements between raters will be discussed in order to reach consensus (involving a third independent member of the research team if necessary).

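### The Sentence Generation score pools pain/neutral homographs with neutral words that have no pain meaning, so general pain-themed writing cannot be told apart from biased interpretation

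*Protocol article*

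**What the plan says.** - **Cue words.** The Sentence generation task section states: "The task included 18 experimental trials featuring nine ambiguous sensory-pain and nine ambiguous neutral stimuli". The Stimuli section says of the neutral homographs: "although they have multiple meanings, none of these were pain-related and so were suitable as neutral training stimuli".
- **Coding.** Under the pilot's Data reduction and analytic plan, a sentence is pain-related if it "describes a painful experience or a situation usually associated with pain". This looks at what the sentence says, not at which meaning of the cue word was used.
- **Score.** The same section continues: "The proportion of pain-related sentences out of total sentences generated was calculated, as in previous research [17". Neither numerator nor denominator is restricted by word type.
- **Main study.** Its Data reduction and analytic plan says: "Data from the Ambiguous Scenarios Task, Sentence Generation Task and ISSA will be processed as discussed above for the pilot study". The one stated exception is that two blinded raters will categorise the sentences.
- **Hypothesis.** Under Aims and hypotheses, hypothesis 2 is about interpretation bias for ambiguous material. Its part 2b is worded more loosely, as the pain group producing more pain-related sentences.

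**The concern.** A neutral homograph gives the participant no pain meaning to choose. A painful sentence about a trailer or about boarding shows that pain is on the writer's mind, not that an ambiguous word was resolved in a pain-related way. The neutral words are in effect the task's control condition, and the score adds them to the signal.

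The pain arm has just worked through 60 training presentations with pain endings (30 scenarios, each shown twice), so some general carry-over into writing is plausible. If it occurs, the pooled score would report it as interpretation bias under hypothesis 2b, and nothing in the score would reveal it. The pilot cannot settle the matter, because it reports only pooled proportions. Elsewhere the plan does separate word types: free recall in the main study is scored by stimulus category.

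**Working it through.** **Inputs from the article.** 9 + 9 cue words; pilot scores 0.28 (SD 0.17) and 0.15 (SD 0.10), nine per group; planned f = 0.244, two-sided alpha 0.05, N = 134. **Assumed:** 67 per group, and every neutral-word rate below, since the article gives none.

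**1. The plan's own figure.** Noncentral F test, df 1 and N − 2, noncentrality N·f². At N = 134 this is 134 × 0.244² = 7.98 and power is 0.8006; 134 is the smallest N that reaches 0.80. The figure reproduces. It corresponds to d = 2f = 0.488. The article gives no separate power figure for the Sentence Generation Task.

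**2. The pilot effect.** d = (0.28 − 0.15) / √((0.17² + 0.10²)/2) = 0.13/0.1395 = 0.93, or 0.83 to 1.04 allowing for rounding. This agrees in size with the printed 1.02. If every pain sentence came from a pain/neutral homograph and all 18 sentences were written, the scores correspond to 18 × 0.28/9 = 56% and 18 × 0.15/9 = 30% of those nine words.

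**3. The denominator.** Let A and B be the pain sentences to the nine pain/neutral homographs and to the nine neutral homographs. Compare A/9 with (A + B)/18. If B = 0, the second is half the first: mean difference and SD both halve, so d and power do not change. A simulation (30% v 42% on the homographs) gives 0.784 for both scores.

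**4. Power when neutral words draw pain sentences at the same rate q in both groups.** d(pooled) = d(nine) × SD(A)/SD(A + B), with SD(A) = 18 × 0.1395 = 2.51, Var(B) = 9q(1 − q) and a correlation of 0 to 0.5 between A and B. Example, q = 5% and correlation 0.5: Var(B) = 0.4275, SD(A + B) = √(6.30 + 0.43 + 1.64) = 2.89, d = 0.488 × 2.51/2.89 = 0.42, power 0.68.

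| q | pooled power, nine-word d = 0.488 (nine-word power 0.80) | pooled power, nine-word d = 0.93 |
|---|---|---|
| 0 | 0.80 | >0.99 |
| 2% | 0.79 to 0.73 | >0.99 |
| 5% | 0.77 to 0.68 | >0.99 |
| 10% | 0.75 to 0.63 | ≥0.99 |

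Models in which one person-level tendency drives both word types lose more. With a logit SD of 0.8 and 30% v 42%, power falls from about 0.79 to 0.71, 0.61 and 0.51 at q = 2%, 5% and 10%. With a probit SD of 0.5 and 30% v 40%, it falls from 0.73 to about 0.63 at q = 3% and 0.47 at q = 10%.

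**5. Attribution.** Suppose the groups do not differ on the pain/neutral homographs, but the pain group writes more pain sentences to neutral words. Share of simulated trials with a significant difference:

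| Neutral-word rate, benign v pain group | pooled score | nine-word score |
|---|---|---|
| 2% v 8% | 33% | 5% |
| 5% v 15% | 55% | 5% |
| 3% v 8% | about 19% | 5% |
| 3% v 12% | about 46% | about 6% |

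The first two rows use the logit model, the last two the probit model. The pooled test is not malfunctioning here: the pooled proportions do differ. The error lies in calling that difference interpretation of ambiguous words.

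**The case against.** Several objections have force.

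- **Power.** A reader might infer that dividing by 18 costs power. It does not (step 3). A loss needs pain sentences to neutral words that add variation without a matching group difference, and the article gives no such rate. If training raises pain content on neutral words too, pooling can raise the rejection rate instead.
- **Attribution rates.** A reader might take the 19% to 55% in step 5 as expected error rates. They assume priming that moves neutral words only. Priming strong enough to put pain into a sentence about a trailer would probably also affect words such as pounding or piercing. For the same reason the nine-word score alone does not remove priming or demand; it is the separate neutral-word result that would show it.
- **Thermal stimuli.** Both arms receive them before this task, so they are no evidence of a difference between arms.
- **Timeouts.** The task section says: "The next trial began after 120 seconds if no response was submitted". The denominator can therefore vary: five pain sentences score 5/18 = 0.28, or 5/15 = 0.33 if three neutral-word trials lapse. But no lapse rate is given and none entered the calculations, so a claim that timeouts add material noise is unsupported.
- **Wording of 2b.** The pooled score matches 2b as literally written. The mismatch is with the construct named in hypothesis 2.
- **Condensation.** The scoring sentence cites earlier work that is not at hand, and the main study's examples both use a pain/neutral homograph, so an unstated restriction to the nine words is possible. The text nevertheless states a rule over all sentences and carries it forward with one named change, so as written it is the pooled rule.

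**Conclusion.** The point holds as one about what the score measures. As written, hypothesis 2b would be tested with a score that counts pain-themed sentences to words with no pain meaning, and general pain-themed writing could not be separated from biased interpretation. Its practical size is unknown, because it rests on neutral-word rates that the article does not report: nil at a rate of zero, negligible for power at the pilot effect, and noticeable only for smaller effects with assumed rates of a few per cent or more. The documents do not support a claim that the denominator itself weakens the test, or that the pilot difference of 0.28 against 0.15 came from neutral words. The task is a secondary outcome and the study was not sized on it, so this is a cheap improvement and not a threat to the main conclusion.

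**What to change.** In the main study's Data reduction and analytic plan:

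- Define the 2b score as pain-related sentences divided by valid sentences, counting only the nine pain/neutral homographs.
- Compute the same proportion for the nine neutral homographs and report it by group as a control for general pain-themed responding.
- If results are to be set beside the pilot, rescore the pilot sentences in the same way.

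The cost is a change of wording. All sentences are already to be collected and rated, so no trial, rating or participant is added. The only drawback is that the new score is not on the scale of the published pilot proportions until those are rescored.

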## Pilot study results

Data was collected from 18 participants (12 female, 5 male, one did not provide data) with a mean age of 25.58 years (SD =  8.55). Nine participants completed benign modification (seven female, two male) and nine completed pain modification (five female, three male, one did not provide data). Table 2 presents descriptive statistics for the self-report measures completed.

**Table 2 pone.0318296.t002:** Descriptive statistics for self-report measures completed in the pilot study (N =  18).

Self-report measure	Benign CBM-I group mean (SD) (n = 9)	Pain CBM-I group mean (SD) (n = 9)
STAI-State	29.44 (4.59)	36.56 (11.37)
STAI-Trait	37.89 (9.83)	41.22 (9.15)
ASI-3 Social	8.11 (3.18)	13.78 (4.94)
ASI-3 Physical	3.44 (3.57)	9.78 (6.5)
ASI-3 Cognitive	1.67 (2.24)	6.44 (3.5)
ASI-3 Total	13.22 (5.63)	30.00 (8.03)
BDI-II	6.33 (4.24)	6.00 (3.64)
SSAS	25.78 (5.33)	29.78 (4.41)
FPQ-III Minor	17.56 (4.82)	20.11 (6.09)
FPQ-III Medical	25.89 (5.16)	25.78 (4.02)
FPQ-III Severe	35.78 (7.66)	38.44 (7.54)
FPQ-III Total	79.22 (12.63)	84.33 (16.53)
PCS Rumination	8.00 (2.00)	8.89 (3.55)
PCS Magnification	3.22 (2.11)	5.56 (2.51)
PCS Helplessness	7.11 (4.23)	12.11 (3.66)
PCS Total	18.33 (7.75)	26.56 (7.97)

ASI =  Anxiety Sensitivity Index; SSAS =  Somatosensory Amplification Scale; FPQ-III =  Fear of Pain Questionnaire-III; PCS =  Pain Catastrophising Scale; BDI-II =  Beck Depression Inventory II; STAI =  State-Trait Anxiety Inventory.

### Task evaluations

For the Ambiguous Scenarios Task, on average 93.70% (SD =  5.07%) of comprehension questions were answered correctly in the learning phase and 97.78% (SD =  6.47%) in the test phase, indicating a high level of engagement. For the Incidental Learning Task, the mean learning congruency effect was -1.63 (SD =  19.78), which indicates responses were slightly faster on incongruent than congruent trials. This suggests that the contingency between word type and dot location was not learnt. For the Interpretation of Ambiguous Sensations Assessment, 120% or 140% of thresholds could not be reached for several participants due to the safety limits of the TSA-II. Specifically, 140% of the pain threshold was higher than 50°C for five participants (3 benign group, 2 pain group) and 120% was higher than 50°C for two participants (1 benign group, 1 pain group).

### Interpretation of ambiguous somatosensory sensations assessment

As shown in Table 3, intensity and unpleasantness ratings were higher for the pain modification group than the benign modification group for stimuli at all threshold percentages. Boxplots for intensity and unpleasantness ratings are shown in Fig 3.

**Table 3 pone.0318296.t003:** Descriptive statistics and between-group differences with effect sizes for intensity and unpleasantness ratings on the interpretation of ambiguous sensations task (N =  18).

Stimulus Type	Benign modification group mean (SD)	Pain modification group mean (SD)	Cohen’s *d*
Intensity Ratings			
60%	16.30 (7.03)	27.22 (21.08)	0.69
80%	22.22 (7.99)	34.48 (19.62)	0.82
100%	38.44 (11.96)	41.11 (16.31)	0.19
120%	54.29 (12.31)	58.08 (12.76)	0.30
140%	52.6 (10.41)	70.75 (11.27)	1.95
Unpleasantness Ratings			
60%	3.59 (6.58)	15.37 (16.22)	0.95
80%	5.04 (8.41)	20.30 (19.81)	1.00
100%	13.89 (13.62)	25.63 (20.77)	0.67
120%	37.29 (26.05)	44.00 (16.68)	0.31
140%	26.53 (24.22)	61.92 (7.14)	3.02

**Fig 3 pone.0318296.g003:**
[figure not shown]
A boxplot showing the intensity and unpleasantness ratings for stimuli at 60% to 140% of the hot pain threshold. The central line indicates the median, the upper and lower ends of the box indicate the upper and lower quartiles of the data. The error bars indicate 1.5 times the interquartile range and dots indicate data points more than 1.5 times above or below the interquartile range beyond either end of the box.

### Assessments of interpretation biases

Pain-related interpretation bias scores on the Ambiguous Scenarios Task were higher for participants in pain modification group (M =  0.44, SD =  4.61) than participants in the benign modification group (M =  -4.44, SD =  4.82), with a large effect size (Cohen’s *d* =  1.03). The interpretation bias index from the Incidental Learning Task did not differ much between the benign modification group (M =  -2.52, SD =  29.76) and the pain modification group (M =  -1.37, SD =  22.26), with a very small effect size (*d* =  -0.05). For the Sentence Generation Task, the proportion of pain-related sentences generated was higher for the pain modification group (M =  0.28, SD =  0.17) than the benign modification group (M =  0.15, SD =  0.10), with a small effect size (*d* =  -1.02). Violin plots for interpretation bias scores for all three paradigms are shown in Fig 4.

**Fig 4 pone.0318296.g004:**
[figure not shown]
Violin plots showing interpretation bias scores on the Ambiguous Scenarios Task, Incidental Learning Task and Sentence Generation Task grouped by interpretation bias modification condition. The width of the violin plots represents the density of the data at each value, with wider sections indicating higher density. Unfilled dots indicate the scores for each individual participant, the black dot indicates the mean across participants, and the error bars represent ± 2 standard deviations.

### Correlational analyses

Anxiety sensitivity was positively associated with unpleasantness ratings for stimuli at 60% (*r* = .51) and 80% (*r* = .51) of the pain threshold. State anxiety was positively associated with intensity ratings for stimuli at 80% (*r* = .48), and 100% (*r* = .48), of the pain threshold, as well as with unpleasantness ratings for stimuli at 60% (*r* = .72), 80% (*r* = .75) and 100% (*r* = .77) of the pain threshold. Trait anxiety was positively associated with intensity ratings for stimuli at 140% (*r* = .48) of the pain threshold, and with unpleasantness ratings for stimuli at 60% (*r* = .61), 80% (*r* = .55), 100% (*r* = .59), 120% (*r* = .56), and 140% (*r* = .54) of the pain threshold. Anxiety sensitivity was positively associated with the proportion of pain sentences generated (*r* = .57). Additionally, scores on the test phase of the Ambiguous Scenarios Task and Sentence Generation Task were correlated (*r* = .68).

